***Assessment and follow up***

Baseline surveys will be done before randomisation when students are in year 8 (age 12/13) in November 2021-March 2022 and will collect data on socio-demographic characteristics, sexual debut and other covariates, drawing on existing survey items.(80) Consent procedures are described under ethics below. Paper questionnaires will be completed confidentially in classrooms supervised by trained fieldworkers, with teachers remaining at the front of the class to maintain quiet and order, but unable to see student responses. Previous experience indicates that paper questionnaires are acceptable and logistically more straightforward than tablet surveys. We will survey absent students by leaving questionnaires and stamped addressed envelopes with schools, and liaising with schools to maximise returns. If schools do not allow face-to-face fieldwork visits, we will instead survey students using an online survey. This will involve students completing online surveys in classrooms supervised by teachers but with teachers remaining at the front of the class to maintain quiet and order, but unable to see student responses, and with fieldworkers available via telephone or internet technology to answer questions in real time. If schools dismiss classes and move to online learning because of Covid infections, we will offer schools the option of surveying students online at home. Schools will send students details of how to log in to surveys using laptops, phones or tablets. Surveys will include links to information boxes explaining key terms informed by the questions students have raised during classroom-based surveys. Students will be asked to skip questions they do not understand or do not wish to answer. Students will be advised to contact their school safeguarding lead for support should they feel confused or upset as a result of completing the questionnaire, with the team briefing safeguarding leads about this and liaising with them to record where this has occurred. We will resurvey students at 33 months (September-December 2024) as students begin year 11 (age 15/16) and will collect self-report data on socio-demographic characteristics, intervention reach/acceptability and outcomes. Survey fieldworkers, but not students, will be blind to allocation. Based on past studies and our pilot,(51, 72, 81) we expect at least 80% survey response rates at baseline and follow-up.

***Process evaluation data collection***

Integral process evaluation informed by existing frameworks(82-85) will examine: intervention fidelity, reach and acceptability and how this varies by school and student; usual treatment in control schools and potential contamination; and implementation processes/intervention mechanisms and how these vary between schools and students.

***Intervention fidelity, reach, acceptability and context:*** Fidelity of implementation of all intervention components by schools and preparatory activities (start-up meetings; training) by SEF will be assessed quantitatively using bespoke measures developed in the pilot RCT. Data will be collected via: audio-recording of SEF training for school staff; surveys of school staff trained by SEF; logbooks of school staff implementing internal training, school health promotion councils, curriculum and social marketing meetings; and structured researcher observations of one randomly selected session per school of internal training, school health promotion councils, curriculum lessons and social-marketing meetings. Across all schools, the RSE coordinator will complete one logbook summarising delivery across the school and teachers will complete one logbook summarising whether the key points of each lesson were taught. In the four case study schools (see below), logbooks will examine delivery of the contents of each lesson in more detail. This approach is informed by the finding from the pilot RCT that collecting detailed information on delivery of every lesson from every teacher is not feasible or acceptable to teachers. Observations will act as a check on the reliability of data from log-books. We will primarily assess fidelity of form (i.e. of activities) but where local adaptations are made we will assess whether these are consistent or not with intervention theory of change in order to provide a qualitative assessment of fidelity of function (i.e. to theory of change).(86) We will examine reach and acceptability to students (overall and by student gender, sexual orientation, ethnicity and SES, and by school-level GCSE attainment and local deprivation) quantitatively via questionnaire survey items at follow-up.

***Comparator and potential contamination:*** We will examine RSE and sexual and reproductive health services provision in and around control schools in order to describe usual treatment. We will examine the potential for contamination across arms to assess whether this is a threat to internal validity. Data will be collected via: student surveys; and structured phone interview with 1 staff-member (using the School Health Research Network school health questionnaire(87)) per control school per year.

***Implementation processes/intervention mechanisms and context:*** Informed by May’s implementation theory and realist evaluation,(83, 85) we will collect qualitative data and analyse these in order to explore implementation processes and intervention mechanisms (beneficial or harmful) and how these vary between schools and students. Data will be collected from all intervention schools via: phone interview with one staff-member and face-to-face focus group with 4-8 students per school (purposive by involvement and gender) per year of delivery. More in-depth data will be collected from 4 case-study schools purposively sampled by GCSE attainment and local deprivation via: phone interview with 4 staff-members and 2 face-to-face focus groups with 4-8 students (purposive by involvement and gender and ethnicity) per year of delivery. It will not be feasible in schools to purposively sample students by sexual orientation or socio-economic status but we will strive to be inclusive of a diversity of students.

***Economic evaluation data collection***

Our economic measure of child health-related quality of life (CHU-9D) is described above.(78) We will undertake a detailed micro-costing of the the intervention, which was found to be feasible in the pilot RCT, including the costs of all components of the intervention described above. Resources to be measured will include: resources used by SEF and schools in terms of staff time, training events/meetings and consumables. Measures will include: standardised sessional checklists to monitor and document attendance, preparation and delivery time for key training events, school health promotion councils, student-run social-marketing meetings and the review of school sexual and reproductive health services; the completion of surveys and diaries by school staff charged with training, curriculum and other intervention delivery; assessing time spent on tasks relating to intervention; and staff travel and other expenses relating to the intervention charged to a specific SEF budget code. Resource use will be valued using market prices. We will also include the costs within the trial period arising from primary and secondary outcomes (valued from published sources, obtained from systematic literature searches), in particular pregnancy, STIs and DRV-related costs, where these are shown to be different between the intervention and control groups. Costs will be presented for each of the perspectives described above.

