**Methods**

***Design***

We will conduct a superiority, phase-III cluster parallel-group RCT to assess whether incorporating Positive Choices into school provision is more effective than usual provision (see figure 1). The trial will comprise 50 schools (minimum 6440, maximum 8500 students) allocated 1:1 to intervention/control assessing primary and secondary outcomes at 33 months using primary intention-to-treat analyses, and using realist approaches to assessing contextual variations in implementation, mechanisms and outcomes.

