***Analytic sample and sample size***

We calculate that, for 80% power with 5% significance, conservatively assuming: a sample of 140 students per school; drop out of 2 schools per arm; 80% student survey response rate at follow-up; an intra-cluster correlation coefficient (ICC) of 0.015 for our primary outcome; and prevalence of this outcome of 9% among those in the control arm, we will require 25 schools per arm to detect a 36% reduction in the primary outcome (giving a prevalence of 5.85% in the intervention arm). The minimum analytic sample for outcome assessment in the RCT will therefore be approximately 6440 students providing follow-up data at 33 months. Repeating this power calculation for the originally intended primary outcome of conceptions (where the prevalence among female controls would be around 2%)(13) would require >100 schools per arm.

These estimates are informed by research and PPI. We assume 140 students per school informed by our recent INCLUSIVE trial.(52) This is a conservative assumption for the Positive Choices trial because the average year group has now risen to 190 and so assuming an 80% response rate (again informed by the Positive Choices pilot and previous studies(42, 52-54)) this would comfortably provide over 150 students.(55) Two schools dropping out is also a conservative assumption given our previous trials have experienced no drop outs.(42, 52, 53) Regarding ICCs, no data are available on school-level clustering of lack of sexual competence at first sex but we would expect this to be very similar to ICCs for non-use of contraception at first sex, which are reported as 0.01(56, 57) so a conservative assumption of 0.015 for this study is reasonable.

Our assumption about prevalence of the primary outcome among controls is also informed by the literature. Around 25% of 15-16 year-olds are sexually active compared with 7% of 12-13 year-olds.(58) Therefore, between baseline and follow-up, we would expect 18% of students to become sexually active. Data from young people participating in the third Natsal sexual behaviour survey suggest that, among those aged 15-16 years, around half lack sexual competence at first sex.(1, 2) Therefore, we would expect around half of trial participants who become sexually active by follow-up (i.e. 9% of all participants) will experience non-competent sexual debut.

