***Economic analyses:*** The aim is to evaluate the cost-effectiveness of Positive Choices versus the comparator from a health and social care perspective as preferred by NICE, additionally considering education and voluntary-sector perspectives.(89) An economic analysis plan will be drafted before receipt of the final data. For our primary cost-utility analysis, costs and CHU-9D data will be combined to present mean cost and quality-adjusted life-years and incremental cost-effectiveness ratios. A secondary cost-consequences analysis will additionally be undertaken for the other trial outcomes as recommended by NICE public health methods guidance(90) because there may not be a strong correlation between CHU-9D and these other outcomes. We will use a multi-level modelling approach with random intercepts to estimate the mean and standard errors for both cost and effects along with the covariance matrix.(91) From these, mean incremental net benefit and confidence intervals will then be estimated. Missing data will be handled using multiple imputation.(92) The time horizon will capture costs and outcomes within the trial. The pilot RCT indicated these analyses as feasible.

***Qualitative data*** will be subject to thematic content analysis (in vivo/axial codes; constant comparison(93)) informed by realist approaches to evaluation(85) and May’s implementation theory(83) to: examine implementation processes, potential intervention mechanisms and how these vary between schools and students. Realist analyses of qualitative data will inform refinements to our theory of change and, where possible, inform additional hypotheses about how context interacts with intervention mechanisms to generate outcomes. These analyses and hypotheses will be posted online prior to assessing them via post hoc exploratory mediation and moderation analyses of quantitative data. In the light of these analyses, we will refine our intervention theory of change, defining what contextual factors promote or impede implementation and mechanisms. This refined theory of change will be the means by which we will make evidence-informed suggestions about the potential for the intervention to be delivered effectively elsewhere.

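### Pregnancy, STI and DRV costs enter the economic analysis only if the arms are shown to differ; read as a 5% test, this rule would set most true pregnancy differences to zero

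*Combined protocol and SAP*

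**What the plan says.** Under *Economic evaluation data collection*, after describing the micro-costing of the intervention, the protocol states: "We will also include the costs within the trial period arising from primary and secondary outcomes". The same sentence says these will be valued from published sources found by systematic searches, and then restricts them: "in particular pregnancy, STIs and DRV-related costs, where these are shown to be different between the intervention and control groups". What counts as showing a difference is not defined by P value, interval or size.

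Under *Data management and analysis*, the economic analyses paragraph plans a multilevel model "to estimate the mean and standard errors for both cost and effects along with the covariance matrix", from which incremental net benefit and its confidence interval follow. The time horizon is the trial period, and no condition on outcome costs is mentioned there. Detail is deferred to an economic analysis plan that is not among the documents. The statistical paragraphs of the same section promise 95% confidence intervals and P values for the secondary outcomes. *Outcome measures* lists pregnancy, STIs and DRV victimisation among these.

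**The concern.** A cost-effectiveness analysis estimates the expected incremental cost and its uncertainty. A difference that has not been demonstrated is imprecise; it is not zero. Dropping a component when its test fails fixes its contribution at exactly zero and removes it from the cost variance and the cost–effect covariance that the model is meant to estimate. Keeping it only when its test succeeds selects the larger estimates.

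The rule bites hardest where events are few. *Analytic sample and sample size* says that powering on conceptions would take more than 100 schools per arm, against 25 here, and the pilot recorded no registered births or terminations. For pregnancy, inclusion would therefore rest on a comparison that the protocol itself describes as underpowered. Cost-effectiveness is research question 4, and averted pregnancies and STIs are part of the economic case in the background. A true cost increase would be hidden in the same way as a true saving.

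**Working it through.** **The plan's own figures first.** The sample size section specifies "for 80% power with 5% significance", "a sample of 140 students per school", "drop out of 2 schools per arm" and "80% student survey response rate at follow-up", with an ICC of 0.015 and 9% prevalence in controls. I assume a two-sided test. Since 46 × 140 = 6,440, the 140 is used as the number responding.

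- Design effect = 1 + (140 − 1) × 0.015 = 3.085. Effective n per arm = 23 × 140 / 3.085 = 1,044.
- Power for 9% v 5.76% (a 36% reduction) is 81%; for 9% v the printed 5.85% it is 78%. The stated 80% is reproduced.
- Conceptions, 2% v 1.28%: 4,884 per arm before clustering. That is 4,884 × 3.085 / 140 = 108 schools per arm, or 142 with 70 girls per school (design effect 2.035). The statement of more than 100 is reproduced.

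**The filter, read as P < 0.05.** With k = 23 schools per arm, m students per school and ICC ρ:

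- n_eff = k·m / [1 + (m − 1)ρ]
- SE = √{[p_C(1 − p_C) + p_I(1 − p_I)] / n_eff}, and μ = (p_C − p_I) / SE
- Chance of passing = Φ(μ − 1.96) + Φ(−μ − 1.96)
- Mean size of a favourable passing estimate, relative to the truth = 1 + φ(1.96 − μ) / [μ·Φ(μ − 1.96)]
- Average share of the true difference counted = the mean of z with non-passing values set to 0, divided by μ

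**Pregnancy.** The 2% in control girls is from the sample size section. Assumed: a 36% reduction (borrowed from the primary outcome), 70 girls per school (half of 140), and ICC 0 to 0.015. The true difference is 0.72 percentage points: about 1,610 × 0.02 = 32 events v 1,610 × 0.0128 = 21.

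| ICC | n_eff per arm | SE (points) | μ | Passes | Set to zero | Ratio to truth if it passes | Mean share counted |
|---|---|---|---|---|---|---|---|
| 0 | 1,610 | 0.447 | 1.61 | 36% | 64% | 1.64 | 60% |
| 0.005 | 1,197 | 0.519 | 1.39 | 28% | 72% | 1.86 | 53% |
| 0.015 | 791 | 0.638 | 1.13 | 20% | 80% | 2.23 | 45% |

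A beta-binomial simulation with a school-level t-test (40,000 runs) at ICC 0.015 gave 20% passing, a ratio of 2.17 and 44% counted. Without the filter, 100% of the true difference was counted on average.

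Varying the inputs over ICC 0.015 to 0: at 1.8% prevalence (the national figure the protocol cites) the chance of passing is 19–33%. With a true 20% reduction it is 9–14%, and favourable passing estimates are 4.0 to 2.9 times the truth.

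**STIs.** The documents give no prevalence. At an assumed 1% of 140 students per school and a 36% reduction, the difference passes 23% of the time (ratio 2.07) at ICC 0.005, and 15% (ratio 2.7) at ICC 0.015.

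**DRV.** *Adolescent sexual health* reports 22–48% among girls, and 12–27% among boys, who have been in a relationship. Assumed: 30% prevalence, 70 relevant students per school, ICC 0.015.

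| True reduction | Passes | Ratio to truth if it passes |
|---|---|---|
| 36% | >99% | 1.00 |
| 20% | 77% | 1.15 |
| 10% | 26% | 1.94 |

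**The case against.** The strongest reply is that the protocol never mentions significance in this sentence. Elsewhere, in reporting the pilot, the authors use the word when they mean it. The pronoun in the condition could refer to the costs, so that any observed difference would qualify. On that reading the clause does almost nothing, and none of the figures above apply. This stands as a limit: the magnitudes depend on the 5% reading. It does not rescue the clause. Either it has no function, or it is a test, or it is a threshold left open unless the economic analysis plan settles it. Each case calls for an edit.

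Second, a reader might infer that all three named costs are rare and would mostly be lost. The documents do not support this for DRV: at the 36% effect used for pregnancy, a DRV difference would almost always pass.

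Third, a reader might take the 1.6–2.2 ratio to mean that savings would be overstated. That ratio holds only among trials that pass; across all trials the rule under-counts.

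Fourth, everything computed here concerns event differences. With no unit costs in the documents, a claim that net benefit is materially wrong cannot be demonstrated.

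Finally, the economic analysis plan, due before the final data arrive, might drop the condition, and the cost-consequences analysis would still display the outcomes. Both soften the consequence, but the protocol text would remain in conflict.

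**Conclusion.** The point holds in a limited form. The inclusion rule is undefined and, read as a 5% test, makes the cost model depend on the outcome results. That is inconsistent with the planned joint estimation of costs and effects over the trial period.

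For pregnancy, a true 36% reduction would be zeroed in about 64–80% of trials, and 45–60% of it would be counted on average. This rests on the plan's 2% and on assumed values for the effect, girls per school and ICC; most true differences are still zeroed at ICC 0. The STI result rests on an assumed prevalence. For DRV the filter mostly zeroes only small effects, of about 10%.

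The consequence for net benefit is established in kind but not in size: an omitted component is treated as a difference known to be zero. The primary effectiveness analysis is unaffected.

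**What to change.** Delete the conditional clause in *Economic evaluation data collection* and align the economic analysis plan with it. Cost every reported pregnancy, STI and DRV event for every analysed student in both arms, whatever the between-arm result, and carry these costs through the multilevel cost–effect model. Report results without these costs as a sensitivity analysis.

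No new data collection is needed, since the events are already survey outcomes. There are two costs. Intervals will be wider. Unit costs must also be sourced for all three outcomes and not only for those that differ; because the valuation searches sit in the same conditional sentence, this may be extra work.

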***Data management and analysis***

Anonymised survey data will be managed by LSHTM’s accredited CTU with linkage to unique identifier codes (not names) in password-protected files on drives accessible only by named CTU staff. The fieldwork team will manage a separate data-file linking names to unique identifiers, in similarly protected files and drives, and will not have access to self-report survey data. This will maintain separation of identifiers and self-report data. Audio-recordings will use secure password-protected recorders. These will be transcribed in full by LSHTM-approved contractors with secure data transfer and management processes. Transcripts will be anonymised and stored in secure files and drives by the fieldwork team. All reporting will be fully anonymised to prevent explicit or implied identification. In line with MRC guidance on personal information in medical research, we will retain all anonymised research data for 20 years after the end of the study. This is to allow secondary analyses and further research to take place, and to allow any queries or concerns about the conduct of the study to be addressed.

A statistical analysis plan will be drafted by the CTU and a data dictionary by the fieldwork team. Statistical analysis of survey data will be led by the CTU, with analysis of fidelity data by the fieldwork team and economic data by [name]. School randomisation and retention, and student response rates will be described using a CONSORT diagram.(88) Baseline and follow-up data will be tabulated by arm. Continuous outcomes will be summarised for each trial arm using means and standard deviations and binary outcomes will be summarised for each trial arm using numbers and percentages. We will conduct intention-to-treat analyses of primary and secondary outcomes (88) as well as exploratory analyses of our intermediate outcomes (RQ1) to estimate intervention effects, reporting 95% confidence intervals and P values for primary and secondary outcomes but not for exploratory analyses of the intermediate outcome. The analytic sample will be students providing follow-up data at 33 months. Analyses will account for school clustering. All outcomes will be analysed using generalised estimating questions (GEEs) with an exchangeable correlation structure and the sandwich estimator of variance to adjust for clustering, with small sample bias correction for the degrees of freedom. For binary outcomes GEEs will be fitted, with a log link to estimate risk ratios and identity link to obtain risk differences. In the event of low prevalence resulting in non-convergence of the GEE model a hierarchical modified Poisson regression model will be used to obtain risk ratios, followed by marginal standardisation to obtain risks for calculating risk differences where required. For continuous outcomes GEEs with an identity link will be used to obtain mean differences.

The primary analysis of all outcomes will include adjustment for stratification factors used in the randomisation. Our primary analysis will be an analysis that is adjusted for the stratification factors only. An additional adjusted analysis will be carried out which will adjust for prespecified cluster level summaries of baseline student age, gender, ethnicity and SES (as measured by the family affluence scale), imputed where feasible from baseline data if missing at follow-up. In addition, any other major imbalances observed between randomised groups will be adjusted for in exploratory secondary analyses. Interim analyses will not be conducted and will not inform intervention modification or discontinuation because this is a cluster RCT with one follow-up wave.

We will undertake exploratory tests of interaction to assess how effects are moderated, including by student gender, sexual orientation, ethnicity and SES as well as by school GCSE attainment and local deprivation (RQ2). These will be exploratory, with limited statistical power. We will also undertake complier-average causal effects analyses to examine how effects are affected by fidelity of implementation (RQ3). Economic analyses will calculate intervention costs and cost-effectiveness (RQ4) (see below). Descriptive statistics will describe fidelity, reach and acceptability using Chi-square tests to examine differences between schools. These will examine whether fidelity differs by school-level GCSE attainment and local deprivation, and whether student-level reach and acceptability differ by student-level gender, sexual orientation, ethnicity and SES. (RQ5). Quantitative and qualitative data from control schools will be analysed to describe usual treatment in control schools (RQ6). Qualitative data will also be used to develop hypotheses about implementation processes/intervention mechanisms and how these might vary between schools or students (RQ7). We will draw on all data to refine the intervention theory of change and draw conclusions about the potential for the intervention to be delivered and be effective elsewhere (RQ8).

***Economic analyses:*** The aim is to evaluate the cost-effectiveness of Positive Choices versus the comparator from a health and social care perspective as preferred by NICE, additionally considering education and voluntary-sector perspectives.(89) An economic analysis plan will be drafted before receipt of the final data. For our primary cost-utility analysis, costs and CHU-9D data will be combined to present mean cost and quality-adjusted life-years and incremental cost-effectiveness ratios. A secondary cost-consequences analysis will additionally be undertaken for the other trial outcomes as recommended by NICE public health methods guidance(90) because there may not be a strong correlation between CHU-9D and these other outcomes. We will use a multi-level modelling approach with random intercepts to estimate the mean and standard errors for both cost and effects along with the covariance matrix.(91) From these, mean incremental net benefit and confidence intervals will then be estimated. Missing data will be handled using multiple imputation.(92) The time horizon will capture costs and outcomes within the trial. The pilot RCT indicated these analyses as feasible.

***Qualitative data*** will be subject to thematic content analysis (in vivo/axial codes; constant comparison(93)) informed by realist approaches to evaluation(85) and May’s implementation theory(83) to: examine implementation processes, potential intervention mechanisms and how these vary between schools and students. Realist analyses of qualitative data will inform refinements to our theory of change and, where possible, inform additional hypotheses about how context interacts with intervention mechanisms to generate outcomes. These analyses and hypotheses will be posted online prior to assessing them via post hoc exploratory mediation and moderation analyses of quantitative data. In the light of these analyses, we will refine our intervention theory of change, defining what contextual factors promote or impede implementation and mechanisms. This refined theory of change will be the means by which we will make evidence-informed suggestions about the potential for the intervention to be delivered effectively elsewhere.

